### Sample size calculation

In the recent recommendations of the International Society of Thrombosis and Hemostasis on studies for PE diagnosis in the ED, it has been suggested that the maximum acceptable failure rate of a tested strategy should not exceed 1.85% [3]. The recent large European prospective cohort studies on PE diagnosis (PROPER, PERCEPIC, YEARS, ADJUST-PE) reported a failure rate of 0.1–0.5%. With an anticipated failure rate of 0.5% in the control group, a non-inferiority margin set at 1.35% (according to the ISTH recommendations so the upper bound of the 95% confidence interval (CI) of the failure rate in the intervention group will not exceed 1.85%), beta = 20%, and one-sided alpha = 2.5%, N1 = 857 patients are needed (East 6, Cytel, Cambridge, MA, USA). Under the assumption of an intra-class correlation coefficient (CCIC) of 0.018, an interperiod correlation (η) of 0.0115 (based on previous cluster randomized trials in French EDs) and a mean cluster size for one period (m) = 22 patients, the cluster design effect would be 1.37 [17, 20]. Considering 5% of non-evaluable patients, with 18 centers and two periods, 1234 patients are needed.

Besides the non-inferiority analysis, it is of utmost importance that the upper bound of the 95% CI of the failure rate of the tested modified diagnostic strategy remains below 1.85%, whatever the rate of the control group is. Our retrospective study reported an anticipated failure rate at 0.85% but focused only on low risk patients. Therefore, with an anticipated failure rate of 1% in the intervention period, the sample size of this group should be at least 700 to respect the maximal upper bound of 1.85%.

Therefore, for a conservative approach to these two conditions (non-inferiority margin at 1.35% and maximal upper bound of the 95% CI below 1.85%), 1400 (700 in each group) subjects will be needed in this study.

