Since this is a non-inferiority study, analysis of the principal criterion will be performed on the per-protocol population (patients without major protocol deviation as no respect of selection criteria, no respect of strategy assigned by randomization, missing values for the principal criteria, or other major protocol deviation identified during data review before freezing of the data base). A sensitivity analysis will be performed on the intention-to-treat population (all randomized patients, except those that withdrew consent). Given the rare occurrence of a thrombo-embolic (TE) event, a generalized linear regression mixed model with Poisson distribution (log link) will be performed (Poisson model for proportions), taking into account a random effect for each center and considering period and strategy-by-period interactions as fixed effects. The decision rule will be based on the upper bound of the 95% two-sided CI of the incidence rates ratio of TE events. Any missing value will be considered as a failure. Secondly, sensitivity analysis will be performed using the 95% two-sided CI of the difference of percentage of TE events between groups. If the upper bound of the CI is above 1.35% of the difference, the inferiority hypothesis of the intervention group will be rejected. Secondary criteria will be compared between groups on the intention-to-treat population and under the superiority hypothesis. The proportions of irradiative imaging, of introduction of anticoagulation regimen, of hospital admission following the ED visit, of all causes of hospital readmission at 3 months, and of all-cause death at 3 months will be compared between groups by using generalized linear regression mixed models with Poisson distribution (log link), taking into account a random effect for each center and considering period and strategy-by-period interaction as fixed effects. If the number of events is sufficient, generalized linear regression mixed modeling with Bernoulli distribution (logit link) will be performed. The proportion difference between groups and its 95% CI will be calculated.

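### The 700 per group that sets the final sample size does not follow from its stated 1% failure rate, and 1400 is not conservative for both planning conditions

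*Protocol article*

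**What the plan says.** The section "beta = 20%, and one-sided alpha = 2.5%, N1 = 857 patients are needed" comes from sizes the trial in two steps.

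The first step is for non-inferiority: "With an anticipated failure rate of 0.5% in the control group, a non-inferiority margin set at 1.35"%, with 80% power and one-sided alpha 2.5%, giving 857. A design effect of 1.37 and 5% non-evaluable patients raise this to 1234. No separate rate for the intervention group is given.

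The second step is a ceiling on the intervention group alone. The text calls it of the highest importance that "the upper bound of the 95% CI of the failure rate of the tested modified diagnostic strategy remains below 1.85"%, whatever happens in the control group. It mentions a retrospective failure rate of 0.85%, notes that it came from low-risk patients only, and moves to a higher value: "with an anticipated failure rate of 1% in the intervention period, the sample size of this group should be at least 700". No interval method, design effect or loss is mentioned for this step.

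The section then settles on 1400, 700 per group, as conservative for both conditions.

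The Statistical analysis plan section of the article states the rule for the primary endpoint: "The decision rule will be based on the upper bound of the 95% two-sided CI of the incidence rates ratio of TE events". A sensitivity analysis uses the difference in percentages and the 1.35-point margin. The 1.85% ceiling is not mentioned there.

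**The concern.** The second step fixes the final sample size, so its arithmetic matters more than that of the first. With about 7 events expected in 700, the choice of interval decides whether the limit lies above or below 1.85%. The two steps also use different failure rates for the same strategy, so one total cannot be called conservative for both without checking it under each rate.

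At stake is what the trial can show about the safety of a raised D-dimer threshold. Readers are told that 700 patients secure the ceiling at 1%. If they do not, the trial may finish unable to meet a condition that its own plan puts first. And if the ceiling is outside the decision rule, non-inferiority could be concluded with the ceiling breached.

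**Working it through.** **Inputs**, all from the Sample size calculation section: control rate 0.5%, margin 1.35 points, one-sided alpha 2.5%, power 80%, design effect 1.37, non-evaluable 5%, ceiling 1.85%, MODS rate 1%, retrospective rate 0.85%, 700 per group.

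**1. Non-inferiority step.** With p = 0.5% in both groups, n per group = 2p(1−p)(1.960 + 0.842)² / 0.0135² = 0.00995 × 7.849 / 0.00018225 = 428.5, a total of 857. The plan's figure is reproduced, but only with equal rates. Then 857 × 1.37 = 1174, and 1174 × 1.05 = 1233 or 1174 / 0.95 = 1236, which brackets 1234.

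**2. Ceiling step at 1% (7/700), 95% upper limit.**
- Wald: 0.01 + 1.96√(0.01 × 0.99/700) = 1.74%.
- Wilson: (0.01 + 0.002744 + 0.007865)/1.005488 = 2.05%.
- Exact (Clopper-Pearson): 2.05%.
- Wald with design effect 1.37: 0.01 + 0.00737 × √1.37 = 1.86%. Exact on the same basis: 2.30%.

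**3. Smallest n with the limit below 1.85%.**

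| Assumed rate | Wald | Wilson | Exact |
|---|---|---|---|
| 1% | 527 | 966 | 967 |
| 0.85% | 324 | 698 | 697 |

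The Wald entry at 1% is 1.96² × 0.0099/0.0085² = 526.4, rounded up. None of the three methods returns 700 at 1%. Exact and Wilson return it almost exactly at 0.85%. At 1%, adding the design effect and then 5% loss gives 967 × 1.37 = 1325 and 1325/0.95 = 1395 by the exact method, or 527 × 1.37 = 722 and 722/0.95 = 760 by Wald.

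**4. Chance of meeting the ceiling with 700 evaluable MODS patients, before clustering.** The exact limit is 1.66% at 5 failures and 1.856% at 6, so 5 or fewer are needed. Binomial P(X ≤ 5) is 30% at a true rate of 1% and 86% at 0.5%. By unadjusted Wald, 7 or fewer are enough, and the probability at 1% is 60%.

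**5. Non-inferiority power with 700 per group**, on the difference scale: Φ{[0.0135 − (pM − pC)] / √([pC(1−pC) + pM(1−pM)]/n) − 1.96}, where C is control and M is MODS. For example, at 0.5% against 1%: 0.0085/0.00461 − 1.96 = −0.116, so 45%. The last column uses n = 700 × 0.95/1.37 = 485.4.

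| Control / MODS | Unadjusted | Design effect 1.37 and 5% loss |
|---|---|---|
| 0.5% / 0.5% | 95% | 85% |
| 1% / 1% | 72% | 56% |
| 0.5% / 1% | 45% | 34% |

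At 0.5% against 1%, 80% power would need about 1,616 per group before clustering and loss.

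**6. Can a comparative rule enforce the ceiling?** Take 7/700 in each group. The upper limit of the difference is 1.96 × √(2 × 0.0099/700) = 1.04 points, or 1.04 × √1.37 = 1.22 with the design effect. Both are under 1.35, while the exact MODS limit is 2.05%. So the non-inferiority criterion can be met with the ceiling breached.

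**The case against.** The article names no interval for the ceiling step. Under an unadjusted Wald limit, 700 at 1% satisfies the condition as written. That stands, and so the point cannot be put as an unconditional arithmetic failure. It does not rescue the figure: Wald would have given 527, it is a poor approximation at 7 events, and it passes 1.85% (by 0.01 points) once the plan's own design effect is applied. The design effect is stated only for the first step, but the same clustered patients supply the MODS rate.

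Four stronger readings are tempting, and the document does not support them.
- That 0.5% and 1% contradict each other. They are planning values for two conditions presented separately, and 0.5% is stated for the control group. They are inconsistent assumptions about MODS, because 857 needs 0.5% there too.
- That the stated 80% power is really 34–45%. The 80% belongs to 857 (1234 after inflation), not to 1400. At 0.5% in both groups, 1400 gives 85–95%. The low figures apply only if MODS doubles the control rate.
- That the authors used 0.85% by mistake. The match is close, but the calculation is not shown. A one-sided 95% Wilson limit at 1% gives 680, which is also near 700, though the text speaks of a 95% CI.
- That the ceiling has been dropped from the analysis. The full analysis plan is not shown and may contain it. What can be said is that the rule printed in the article is comparative and cannot by itself enforce a ceiling meant to hold at any control rate.

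**Conclusion.** The point holds in this form. The group size of 700 does not follow from the stated 1% rate: the exact or Wilson upper limit is 2.05% against a ceiling of 1.85%, and about 967 patients would be needed before clustering or loss. The description of 1400 as conservative for both conditions fails at the plan's own 1% for MODS. There the chance of meeting the ceiling is 30%, and non-inferiority power is 45% (34% with clustering and loss) if the control rate is 0.5%.

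The trial is well placed if the true rate is 0.5% in both groups: 86% for the ceiling before clustering, and 85–95% for non-inferiority.

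These figures assume an exact or Wilson two-sided 95% limit, 700 evaluable MODS patients, the design effect of 1.37 as stated where clustering is included, and a normal approximation for power on the difference. Because the endpoint counts only patients in whom PE was initially ruled out, 700 enrolled will yield fewer than 700 evaluable. The article gives no index-PE proportion, so I have not put a number on that.

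**What to change.** Keep 1400 and change the text.

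1. In the sample size section, name the interval for the ceiling (exact or Wilson, with allowance for clustering).
2. Replace the statement that 700 suffices at 1% with the actual properties: with 700 evaluable MODS patients and before clustering, 5 or fewer failures keep the exact limit below 1.85%, with probability 30% at a true rate of 1% and 86% at 0.5%.
3. State that 857 assumes 0.5% in both groups. Give the non-inferiority power of 700 per group on the 1.35-point difference: 95%, 72% and 45% for 0.5%/0.5%, 1%/1% and 0.5%/1% (control/MODS), or 85%, 56% and 34% with design effect 1.37 and 5% loss.
4. Remove or requalify the claim that 1400 is conservative for both conditions.
5. Add to the decision rule that a conclusion of safety also requires the MODS upper limit to be below 1.85%, alongside the non-inferiority criterion. This addition leaves the scale of that criterion as it is.

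The cost is wording in the protocol and analysis plan, with no extra patients. The stated properties become less favourable, and item 5 makes a conclusion of safety harder to reach, so it should be settled before the database is frozen.

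### The 700 MODS patients do not follow from the stated 1% failure rate and 1.85% ceiling: exact or Wilson limits need about 967, and only a Wald interval that ignores clustering meets the ceiling at 700

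*Protocol article*

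**What the plan says.** The Sample size calculation section of the Protocol article sets two conditions.

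The first is non-inferiority with a 1.35% margin at a 0.5% control failure rate: "beta = 20%, and one-sided alpha = 2.5%, N1 = 857 patients are needed". For clustering, "the cluster design effect would be 1.37", and then: "Considering 5% of non-evaluable patients, with 18 centers and two periods, 1234 patients are needed".

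The second is a ceiling on the intervention group alone, which the section ranks as a paramount requirement whatever the control rate turns out to be: that "the upper bound of the 95% CI of the failure rate of the tested modified diagnostic strategy remains below 1.85" per cent. On the rate to plan for, it says: "Our retrospective study reported an anticipated failure rate at 0.85% but focused only on low risk patients". It therefore moves to a higher rate and concludes that "with an anticipated failure rate of 1% in the intervention period, the sample size of this group should be at least 700".

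Taking the larger of the two sizes, the section ends with "1400 (700 in each group) subjects will be needed in this study". It names no interval method for the ceiling, shows no allowance for clustering or loss in the 700, and claims no probability of meeting the ceiling.

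**The concern.** The non-inferiority condition needs 1234 patients, so the ceiling condition fixes the trial at 1400. The 700 is presented as the size at which a MODS group failing at 1% stays under the limit. At that rate 700 patients yield seven failures, and with so few events the upper confidence limit lies well above the point estimate. If the 700 does not follow from the 1%, readers will believe the trial can show MODS to be below 1.85% at its anticipated failure rate when, under the usual intervals for rare events, it is not large enough to do so.

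**Working it through.** **Inputs**, all from Sample size calculation: ceiling U = 1.85%; anticipated rate p = 1%; n = 700; retrospective rate 0.85%; design effect 1.37; 5% non-evaluable. The level is two-sided 95%. This matches the one-sided 2.5% in the same section and the two-sided 95% interval in Statistical analysis plan.

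**Check that the section's other figure reproduces.** Non-inferiority size per group = 2 × 0.005 × 0.995 × (1.96 + 0.8416)² / 0.0135² = 428.5, so 857 in total, as stated.

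**Upper bound at 1% of 700, i.e. 7 failures.**
- Clopper-Pearson: the 97.5% quantile of Beta(8, 693) = 2.05%.
- Wilson: [0.01 + 3.8415/1400 + 1.96 × √(0.0099/700 + 3.8415/(4 × 700²))] / (1 + 3.8415/700) = 0.02061/1.00549 = 2.05%.
- Wald: 0.01 + 1.96 × √(0.0099/700) = 0.01 + 0.00737 = 1.74%.

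**Size that brings the bound to 1.85% at 1%.**
- Wilson: n = z²U(1 − U)/(U − p)² = 3.8415 × 0.0185 × 0.9815 / 0.0085² = 965.4, so 966.
- Wald: n = z²p(1 − p)/(U − p)² = 3.8415 × 0.0099 / 0.0085² = 526.4, so 527.
- Clopper-Pearson, by search: 967.

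**All two-sided 95% intervals tried, without clustering or loss:**

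| Interval | Bound at 7/700 | n needed at 1% | Most failures allowed in 700 | Chance of meeting ceiling at a true 1% |
|---|---|---|---|---|
| Clopper-Pearson | 2.05% | 967 | 5 | 30% |
| Wilson | 2.05% | 966 | 5 | 30% |
| Exact Poisson | 2.06% | 981 | 5 | 30% |
| Agresti-Coull | 2.09% | 1014 | 5 | 30% |
| Jeffreys | 1.95% | 844 | 6 | 45% |
| Wald, continuity-corrected | 1.81% | 639 | 7 | 60% |
| Wald | 1.74% | 527 | 7 | 60% |

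The required sizes run from 527 to 1014, and none is 700. The last column is the binomial probability of at most that many failures in 700: P(X ≤ 5) = 0.299, P(X ≤ 6) = 0.449, P(X ≤ 7) = 0.599. For Clopper-Pearson, 5/700 gives 1.66% and 6/700 gives 1.856%, so five is the most that passes.

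**With the plan's design effect.** 700/1.37 is about 511 effective patients. Wald: 0.01 + 0.00737 × √1.37 = 1.86%, and the required size is 526.4 × 1.37 = 721.2, so 722. Clopper-Pearson at the same effective size: 2.30%. Taking off 5% for non-evaluable patients as well (665/1.37 = 485) gives 1.89% for Wald.

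**The same size at 0.85%.** Wilson: 3.8415 × 0.0185 × 0.9815 / 0.01² = 697.5, so 698; Clopper-Pearson 697.

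**Chance of meeting the ceiling with 700, by true rate (0.5%, 0.85%, 1%):** exact or Wilson 86%, 45%, 30%; Jeffreys 94%, 61%, 45%; Wald 97%, 75%, 60%.

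**The case against.** The strongest defence is that no interval is named. The article refers to a full protocol and analysis plan in its supplementary files, where a method may be given. Under a plain Wald interval 7/700 gives 1.74%, and continuity-corrected Wald gives 1.81%; 700 then is at least enough and the sentence is true. This stands as far as it goes, so it would be too strong to say without qualification that 700 patients breach the ceiling at 1%, or that the chance of meeting it is simply 30%. It does not rescue the figure, because Wald would have given 527, is unreliable at about seven events, and misses the ceiling once the plan's 1.37 is applied.

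One could answer that a design effect with full credit for the cross-over is smaller. The plan's inputs give 1 + 21 × 0.018 − 22 × 0.0115 = 1.125, and Wald is then 1.78%. That credit belongs to the comparison between periods. For the rate in one group, the within-period form 1 + 21 × 0.018 = 1.378 applies, close to the plan's 1.37.

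A one-sided 95% Wilson bound at 1% gives 680, near 700, but that is not the level used elsewhere in the article.

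A reader might infer that 700 was computed from 0.85% and left in place when the rate was raised to 1%. The match (697 or 698) makes this possible, but the article does not say so. The match also rests on 0.0085 × 700 = 5.95 failures; the nearest whole count, 6/700, gives 1.856% and just misses.

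Finally, sizing on the expected bound is a common precision approach, and the 80% power is stated only for non-inferiority. The lack of a stated probability for the ceiling is therefore not in itself an arithmetic error.

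**Conclusion.** The figure is wrong as written: 700 is not the size that a 1% failure rate and a 1.85% ceiling imply under any two-sided 95% interval tried. Under exact or Wilson limits the expected bound is 2.05%, and the matching size is about 967, or 267 more than stated. Only a Wald interval that ignores clustering meets the ceiling at 700.

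The chance of meeting the ceiling at a true 1% is between 30% and 60% depending on the interval. This assumes 700 independent, evaluable patients and no loss.

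The consequence is limited to the ceiling claim. The formal decision rule is comparative ("The decision rule will be based on the upper bound of the 95% two-sided CI of the incidence rates ratio of TE events"), and 1400 exceeds the 1234 given for non-inferiority, so nothing here shows that the non-inferiority comparison is undersized. The paragraph still needs correcting, because the ceiling is given the highest importance and this figure sets the trial's size.

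**What to change.** Rewrite the ceiling paragraph of Sample size calculation so that rate, size and interval agree:

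- Name the interval for the MODS failure rate, exact (Clopper-Pearson) or Wilson.
- State that at 1% with 700 patients the expected upper bound is 2.05%, and that about 967 patients would match the ceiling.
- State whether clustering is allowed for in this bound.
- Give the chance of meeting the ceiling with 700 patients: 86%, 45% and 30% at true rates of 0.5%, 0.85% and 1% (exact or Wilson, at most 5 failures, before clustering and loss).
- If the sponsor's records show that 700 was derived from 0.85%, say so; otherwise do not attribute it to that rate.

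Enrolment stays at 1400. The cost is the rewording of one paragraph and a stated figure that is less favourable than the present one.

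### The non-inferiority sample size assumes a 0.5% MODS failure rate, the ceiling condition anticipates 1%, and at 1% against a 0.5% control the 1400 patients give about 35–45% power on the risk-difference margin

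*Protocol article*

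**What the plan says.** All of this stands in the Sample size calculation section of the protocol article.

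- **Non-inferiority condition.** It starts "With an anticipated failure rate of 0.5% in the control group", with "a non-inferiority margin set at 1.35" percent and "beta = 20%, and one-sided alpha = 2.5" percent, and concludes that "N1 = 857 patients are needed". No MODS rate is given here. A design effect of 1.37 and 5% non-evaluable patients raise the total to 1234.
- **Ceiling condition.** The upper 95% confidence bound of the MODS failure rate must stay below 1.85%, whatever the control rate. The section mentions the group's own retrospective estimate of 0.85%, notes that it covered low-risk patients only, and on that ground sizes the MODS group "with an anticipated failure rate of 1% in the intervention period". The result is at least 700 patients in that group.
- **Conclusion.** The total is set at 1400, 700 per group, "for a conservative approach to these two conditions".

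**The concern.** The MODS failure rate is a single unknown. If the plan's own data lead it to expect 1%, that expectation applies to the comparison with control as much as to the ceiling. Against a control rate of 0.5%, a 1% MODS rate uses 0.5 of the 1.35 points of margin before any sampling error, and it also increases the variance. The section never asks what 1400 patients deliver for non-inferiority in that case.

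At stake is how a result will be read. A reader told that the size achieves 80% power and is conservative on both counts would take a failure to show non-inferiority as evidence against MODS. Under the anticipated rate, such a failure could well come from limited power.

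**Working it through.** **Inputs from the Sample size calculation section:** control rate 0.5%; margin 1.35 points; one-sided alpha 2.5% (z = 1.96); power 80% (z = 0.8416); MODS rate 1% (ceiling condition); retrospective MODS estimate 0.85%; 700 per arm; design effect 1.37.

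**Step 1: reproduce 857.** The unpooled formula is n per arm = (1.96 + 0.8416)² × [pC(1−pC) + pT(1−pT)] / (margin − (pT − pC))².

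- Both arms at 0.5%: 7.849 × (0.004975 + 0.004975) / 0.0135² = 428.5 per arm, total 857. This matches.
- 857 × 1.37 / 0.95 = 1236, or 857 × 1.37 × 1.05 = 1233. The stated 1234 lies between them.
- Control 0.5%, MODS 1%: 7.849 × (0.004975 + 0.0099) / 0.0085² = 1616 per arm, 3232 in total before any inflation.

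So 857 rests on equal rates of 0.5%. This is inferred from the match, because the section states 0.5% for control only.

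**Step 2: power of 700 per arm.** Power = Φ[(margin − (pT − pC)) / SE − 1.96], with SE = √{[pC(1−pC) + pT(1−pT)] / n}. The design effect enters as n = 700 / 1.37 = 510.9.

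Worked case, control 0.5% and MODS 1%:
- n = 700: SE = √(0.014875 / 700) = 0.00461; 0.0085 / 0.00461 − 1.96 = −0.116; power 45%.
- n = 510.9: SE = 0.00540; 0.0085 / 0.00540 − 1.96 = −0.385; power 35%.

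| Control | MODS | Power, no design effect | Power, design effect 1.37 |
|---|---|---|---|
| 0.5% | 0.5% | 95% | 86% |
| 0.5% | 0.85% | 63% | 50% |
| 0.5% | 1% | 45% | 35% |
| 1% (not stated in the plan) | 1% | 72% | 58% |

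Removing 5% non-evaluable patients (665 per arm) changes the 0.5% versus 1% row to 43% and 34%.

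**Step 3: meeting both conditions.** The section names no interval method. With Wald intervals throughout, 7 events in 700 give an upper bound of 0.0100 + 1.96 × √(0.01 × 0.99 / 700) = 1.74%, which passes. Eight events give 1.93%, which does not. So the ceiling is met with 7 or fewer MODS events. Exact binomial enumeration at 700 per arm, without clustering, gives:

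| Control / MODS | Non-inferiority (Wald) | Ceiling (Wald) | Both |
|---|---|---|---|
| 0.5% / 0.5% | 92% | 97% | 92% |
| 0.5% / 1% | 46% | 60% | 44% |

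The interval method matters. The exact (Clopper–Pearson) upper bound for 7/700 is 2.05%, above the ceiling.

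**The case against.** - **Equal true rates are the usual basis for a non-inferiority sample size, and the calculation on that basis is right.** This stands: 857 reproduces, and 1400 gives 86–95% power under that assumption. A reader might infer that the plan has abandoned the equal-rate scenario, so that its 80% applies to nothing it believes. The text does not support that. It keeps both conditions and takes the larger number. The convention does not settle the matter, though, because the plan itself anticipates a higher rate for the same arm.
- **The 1% may be just a cautious input to a separate precision requirement.** The ceiling condition is indeed framed apart from the non-inferiority test and as independent of control. But the 1% is described as anticipated, and its justification, a retrospective 0.85% limited to low-risk patients, concerns the true MODS rate. Caution applied to the ceiling does not make the size conservative for the comparison.
- **The pairing of 0.5% with 1% is never stated as a scenario.** This is true, and the lowest figures depend on it. A higher-risk population could raise the control rate too. The only control rate given is 0.5%, however, and with control also at 1% power is still 72% (58%).
- **The design effect is open to question.** The stated 1.37 is close to the parallel-cluster form, 1 + 21 × 0.018 = 1.378. Using the interperiod correlation as well gives 1 + 21 × 0.018 − 22 × 0.0115 = 1.125, and power at 0.5% versus 1% of 41%. That lies within the 35–45% range.
- **The primary decision uses another scale.** The Statistical analysis plan section bases it on the incidence rate ratio and makes the percentage difference a sensitivity analysis. A reader might infer that the primary analysis will more often miss non-inferiority than show it. These calculations do not establish that. They address the difference-scale margin, which is the margin the sample size was built on.

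**Conclusion.** The section is inconsistent as written. Its non-inferiority size implies a MODS rate of 0.5%, its ceiling condition anticipates 1%, and the claim of a conservative size covers both although non-inferiority was never checked at 1%.

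On the risk-difference margin with 700 per arm, power falls from 86–95% at equal 0.5% rates to 50–63% at the retrospective 0.85% and to 35–45% at the anticipated 1%. The range in each case is with and without the stated design effect. The chance of meeting both conditions at 0.5% versus 1% is about 44% with Wald intervals and no clustering.

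This rests on four assumptions: control stays at 0.5%, the unpooled formula inferred from 857 is the one used, 700 per arm are analysed, and the decision is made on the difference scale. Raising control to 1% softens the result but does not restore 80%. The plan does not claim 80% power at a 1% MODS rate. The fault is that the section leaves the reader to assume it.

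**What to change.** Revise the Sample size calculation section as follows:

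1. State the MODS rate used in the non-inferiority condition, and carry the anticipated 1% into it.
2. Give the power of the 1400 patients in a short table for MODS at 0.5%, 0.85% and 1% against control at 0.5%, with a sensitivity row for a higher control rate and with the design effect shown.
3. Report the probability of meeting both conditions together, and name the interval method for each.
4. State that power of at least 80% holds only if MODS and control fail about equally often.
5. Stop describing 1400 as conservative for the non-inferiority condition, and say that these figures refer to the difference-scale margin and not to the rate-ratio rule.

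The cost is one corrected paragraph and a small table. The stated power becomes less favourable under the plan's own 1%. Enrolment, margin, endpoint and analysis are unchanged.
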